## Abstract

**Objectives:**

The primary objective of the presented study is to analyze the respiratory and functional effects of a rehabilitation program in patients affected by hospitalization in Intensive Care Unit (ICU) due to COVID-19, in comparison with the group treated with standard of care, at discharge endpoint.

The secondary objectives of the presented study are to evaluate different outcomes of the rehabilitation program in comparison to standard of care regarding: functional performance at 4-week and 12-week post- discharge mark; health-related quality of life, the impact on the health services (namely days of hospitalization), the cost-effectiveness of the intervention proposed.

**Trial design:**

This is a randomized, controlled, double-blind, double-arm clinical trial of treatment, with an allocation ratio 1:1 and framework of superiority.

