**Intervention and comparator:**

Both groups will receive usual medical and nursing care in the ICU, which involves assessment and treatment of the respiratory system and may include positioning, hyperinflation techniques and suctioning. The physical function of the patient is assessed, and active bed exercises and mobility are encouraged as soon as possible and may include sitting out of bed.

The intervention group will receive a functional and respiratory multidisciplinary rehabilitation protocol (that includes medical, nursing, physiotherapy and occupational therapy interventions) during their entire hospital stay.

After reassurance that the patients fulfil the safety criteria, they will initiate the rehabilitation protocol, individualized to each patient based on the clinical status. The rehabilitation interventions and exercises implemented will be consistent with recommendations from the Portuguese Society of Physical Rehabilitation Medicine.

The intervention will occur 6 days per week (Monday to Saturday), fifteen minutes, twice per day for each participant. Throughout all activities, progression will be increased successively, depending on the individual’s tolerance and stability.

After discharge, the intervention group will continue with rehabilitation exercises, prescribed by physical rehabilitation doctors. These exercises are designed for the patient to do at home, and then report their execution to rehabilitation nurses through teleconsultation, until 12 weeks after ICU discharge.

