**Blinding (masking):**

The evaluators in the study will be blinded during the entire process. The evaluators will be unaware of the study objectives and the randomized distribution of patients to study groups and will not have access to the randomization sequence. Although blinding for patients will not be possible to achieve completely, subjects will be unaware of other treatment modalities, and they will not know if they belong to the intervention or standard group. As for the treating physiotherapists and ICU staff, blinding will not be possible to achieve, but they will not be responsible for assessing outcomes.

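### The trial is labelled double-blind, but by its own account only the evaluators are blinded without reservation, so its patient-rated outcomes lack assured patient blinding

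*Protocol article*

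**What the plan says.** The protocol article addresses blinding in two places.

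- **Trial design:** "This is a randomized, controlled, double-blind, double-arm clinical trial of treatment".
- **Blinding (masking), evaluators:** "The evaluators in the study will be blinded during the entire process". They are also said not to know the study objectives or the allocation, and to have no access to the randomisation sequence.
- **Blinding (masking), patients:** "Although blinding for patients will not be possible to achieve completely, subjects will be unaware of other treatment modalities". The sentence then adds that "they will not know if they belong to the intervention or standard group".
- **Blinding (masking), treating staff:** "As for the treating physiotherapists and ICU staff, blinding will not be possible to achieve, but they will not be responsible for assessing outcomes".

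Intervention and comparator describes usual ICU care for both groups, including active bed exercises and encouragement to mobilise. The multidisciplinary programme is for the intervention group: fifteen minutes twice a day, Monday to Saturday, throughout the hospital stay. After discharge that group does prescribed exercises at home and is to "report their execution to rehabilitation nurses through teleconsultation, until 12 weeks after ICU discharge".

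Main outcomes names the 6-Minute Walk Test as primary measure (discharge, 4 and 12 weeks). The Medical Research Council Sum-Score, handgrip strength, the dyspnoea scale and the Borg rating are measured at discharge and repeated at 4 and 12 weeks. The SF-12 is measured at 12 weeks.

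**The concern.** The design line claims a property that the blinding section then withdraws. If treating staff are unblinded and patient blinding is incomplete, the label can be defended only by counting patients as the second blinded party, and the article says that this blinding is not fully achieved.

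The label matters because of who produces the data. A blinded evaluator protects a measurement against the evaluator's expectations. It does not protect an answer that the patient gives about breathlessness, exertion or quality of life. Quality of life is a stated secondary objective. If the results are presented as double-blind, a between-group difference in these ratings may be credited with masking that the design does not assure. To a lesser degree the same applies to tests that depend on how hard the patient tries, including the primary walk test.

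**Working it through.** No arithmetic on a stated figure applies. The check sets the article's statements side by side.

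**1. Who is blinded, by role (Blinding section)**

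- Evaluators: blinded throughout, without reservation.
- Treating physiotherapists and ICU staff: not blinded.
- Patients: not completely blinded. What is withheld is information about the other treatment.

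One of the three roles is blinded without qualification, one is unblinded and one is partial. That is an evaluator-blinded design with some withholding of information from patients.

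**2. Whether the statement that patients will not know their group can stand**

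It sits in the same sentence as the concession that patient blinding is incomplete, so the sentence pulls two ways. Set against Intervention and comparator:

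- *In hospital.* The programme described for the intervention group amounts to 2 × 15 = 30 minutes a day, and 30 × 6 = 180 minutes a week. Both groups receive respiratory treatment, bed exercises and encouragement to mobilise, so the visible contrast is one of degree.
- *After discharge.* Home exercises and reporting by teleconsultation are described for the intervention group only, up to 12 weeks after ICU discharge. No sham or attention control is described for the standard-care group.

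Not telling patients what the other group receives may hide the comparison from them. It does not hide from a patient that he or she is doing a prescribed programme and reporting on it for weeks. The contrast is plainest after discharge.

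**3. Which outcomes this touches (Main outcomes)**

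Six measures are named for follow-up:

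- *Supplied by the patient (3):* SF-12 at 12 weeks; dyspnoea scale and Borg rating at discharge, 4 and 12 weeks.
- *Evaluator-assessed but effort-dependent (3):* 6-Minute Walk Test, Medical Research Council Sum-Score and handgrip strength, at discharge, 4 and 12 weeks.

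Evaluator blinding does not protect the first three. For the other three it protects the reading of the test but not the patient's effort.

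**4. Timing**

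The Objectives section sets the primary comparison at discharge. Home exercise and teleconsultation begin afterwards. They therefore bear on the 4- and 12-week measures, including the only SF-12 assessment, and not on the walk test at discharge. For the discharge measures, the relevant facts are the in-hospital programme and the article's own concession on patient blinding.

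**The case against.** The strongest reply is that nothing is concealed. The Blinding section sets out the limits role by role, in a short article where a reader of the label will also meet the qualification. Full blinding of patients and therapists is seldom feasible in a rehabilitation trial. The label also has a discernible basis: evaluators are masked, and patients are partly masked because they are not told about the other treatment. A patient may know that he or she is exercising without knowing that this is the experimental arm.

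Much of this stands, and it sets the limits of the point. Disclosure in one section, however, does not make a contrary label in another correct, and the disclosing section itself adds an assurance about patients that it cannot support. That the article condenses a full protocol is no answer either: the point is a conflict between printed statements, not missing detail.

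Three stronger readings are tempting and are not supported:

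- *That patients are simply unblinded, or that the patient-rated outcomes are open-label.* The article claims partial masking through withheld information. What it supports is that blinding is incomplete and not assured.
- *That the primary comparison at discharge is undermined by the home programme.* That programme starts after discharge, and the walk test is assessed by blinded evaluators.
- *That the registry entry misleads its readers.* The article gives only the registration number, title and date. What the registry says about masking is not shown.

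**Conclusion.** The double-blind label is wrong as written, and the statement that patients will not know their group is unsupported. On the article's own account, the evaluators are the only party whose blinding is stated without reservation.

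The consequence is limited but real. Three of the six follow-up measures are patient-supplied and should not be read as double-blind evidence, above all at 4 and 12 weeks. The other three, the primary walk test among them, keep the real benefit of blinded evaluators, with a caveat about effort. The article gives no basis for stating a direction or size of bias, and none is claimed.

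The conclusion on the label follows directly from the printed text. The conclusion on the clause about patients also assumes that the standard-care group receives no comparable home programme or contact. None is described in the article; the full protocol is not at hand.

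This is a correction of labelling and interpretation. It does not call into question the allocation, endpoints, sample size or analysis.

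**What to change.** - In Trial design, replace double-blind with wording such as: *evaluator-blinded; treating staff not blinded, patient blinding incomplete*.
- In Blinding (masking), delete the clause saying that patients will not know their group, or limit it to what is actually done: *patients are not told what the other group receives*.
- State that SF-12, dyspnoea and Borg results will be interpreted as patient-reported outcomes without assured patient blinding.
- Optionally, have evaluators record at each follow-up whether they learned the allocation, since patients who know their regimen may disclose it. This is an added safeguard; its absence from a condensed article is not a fault.
- Align the registry record only if it carries the same label.

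The cost is a change of wording and, if the option is taken up, one tick-box on the assessment form. The downside is that the stated design looks slightly less favourable. Evaluator blinding is a real strength and stays as it is.

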**Participants:**

The study will be conducted at Centro Hospitalar Entre Douro e Vouga, Santa Maria da Feira, Portugal. Potential participants will be adult patients (≥18 years old) hospitalized in ICU with respiratory insufficiency due to COVID-19, who are referred to respiratory and functional rehabilitation. Only patients approved by physical rehabilitation doctors to perform respiratory and functional rehabilitation will be considered potential participants. To be eligible for inclusion participants must have been independent in their activities of daily living before the onset of critical illness (verbal statement by their proxy) and have to meet the safety criteria defined by the Portuguese Society of Physical Rehabilitation Medicine.

**Intervention and comparator:**

Both groups will receive usual medical and nursing care in the ICU, which involves assessment and treatment of the respiratory system and may include positioning, hyperinflation techniques and suctioning. The physical function of the patient is assessed, and active bed exercises and mobility are encouraged as soon as possible and may include sitting out of bed.

The intervention group will receive a functional and respiratory multidisciplinary rehabilitation protocol (that includes medical, nursing, physiotherapy and occupational therapy interventions) during their entire hospital stay.

After reassurance that the patients fulfil the safety criteria, they will initiate the rehabilitation protocol, individualized to each patient based on the clinical status. The rehabilitation interventions and exercises implemented will be consistent with recommendations from the Portuguese Society of Physical Rehabilitation Medicine.

The intervention will occur 6 days per week (Monday to Saturday), fifteen minutes, twice per day for each participant. Throughout all activities, progression will be increased successively, depending on the individual’s tolerance and stability.

After discharge, the intervention group will continue with rehabilitation exercises, prescribed by physical rehabilitation doctors. These exercises are designed for the patient to do at home, and then report their execution to rehabilitation nurses through teleconsultation, until 12 weeks after ICU discharge.

**Main outcomes:**

Baseline descriptive data collection will include age, sex, comorbidities and date of admission to ICU. The need of mechanical ventilation and length of use, as well as the need for oxygen therapy, length of ICU stay (days/hours), incidence of ICU readmission, discharge destination and survival will also be recorded.

Prior to intervention, every two days and at discharge, participants will be evaluated using the following scales: Glasgow Coma Scale, Richmond Agitation Sedation Scale, Chelsea Critical Care Physical Assessment, 5 standardized questions for cooperation, Medical Research Council Sum-Score, Handgrip strength test and Medical Research Council dyspnea scale. At discharge, Borg Rating of Perceived Exertion will be evaluated.

The primary outcome measure will be functional capacity using the 6-Minute Walk Test, and it will be measured at discharge and at the 4-week and 12-week mark. Medical Research Council Sum-Score, Handgrip strength test, Medical Research Council dyspnea scale and Borg Rating of Perceived Exertion will also be re-evaluated at the 4-week and 12-week mark. The health related quality of life will also be used as an outcome measure, using the 12-Item Short Form Survey, at 12 weeks of follow-up.

**Randomisation:**

Participants will be divided into two groups, standard care and intervention, by means of balanced randomization at a 1:1 ratio using blocks of 10 participants. The randomization sequence is going to be created using a free software (http://www.randomized.org/). In order to ensure the confidentiality of the randomisation sequence, this process will be conducted by an assessor external to the study.

**Blinding (masking):**

The evaluators in the study will be blinded during the entire process. The evaluators will be unaware of the study objectives and the randomized distribution of patients to study groups and will not have access to the randomization sequence. Although blinding for patients will not be possible to achieve completely, subjects will be unaware of other treatment modalities, and they will not know if they belong to the intervention or standard group. As for the treating physiotherapists and ICU staff, blinding will not be possible to achieve, but they will not be responsible for assessing outcomes.

**Numbers to be randomised (sample size):**

We plan to randomise 40 participants to each group. 80 participants in total.

**Trial Status:**

This is the second and definitive protocol version, dated from 26th February 2021. Recruitment started on 8^th^ March 2021. Participants will be recruited between March 8, 2021, and June 8, 2021. Study completion is expected to be October 2021.

**Trial registration:**

ReBEC RBR-7rvhpq9. Registry name: The effect of rehabilitation in hospitalized COVID-19 patients. Registered on 17 March 2021.Retrospectively registered.

**Full protocol:**

“The full protocol is attached as an additional file, accessible from the Trials website (Additional file 1). In the interest in expediting dissemination of this material, the familiar formatting has been eliminated; this Letter serves as a summary of the key elements of the full protocol”.

**Supplementary Information:**

The online version contains supplementary material available at 10.1186/s13063-021-05210-y.

## Data Availability

The datasets analyzed during the current study are available from the corresponding author on reasonable request. The data will be available after the main publication of them; for other circumstances, they should consult the corresponding author. Any data required to support the protocol can be supplied on request.
